## Abstract

**Background:**

Musculoskeletal injury (MSKI) is the leading cause of medical downgrading and discharge within the UK military, with lower limb MSKI having the greatest incidence, negatively impacting operational readiness. Pain is a primary limiting factor to rehabilitation progress following MSKI. Heavy-load resistance training (RT; ie, loads >70% 1-repetition maximum) is traditionally used but may be contraindicated due to pain, potentially prolonging recovery and leading to failure of essential physical employment standards for UK military personnel. Low-load RT with blood flow restriction (BFR) can promote favourable morphological and physiological adaption, as well as elicit hypoalgesia in healthy and clinical populations (eg, post-operative), and has proven a viable option in military rehabilitation settings. The acceptability and tolerance of higher relative BFR pressures in persistent pain populations are unknown due to the complexity of presentation and the perception of discomfort experienced during BFR exercise. Greater relative pressures (ie, 80% limb occlusion pressure (LOP)) elicit a greater hypoalgesic response in pain-free individuals, but greater perceived discomfort which may not be tolerated in persistent pain populations. However, lower relative pressure (ie, 40% LOP) has elicited hypoalgesia in pain-free individuals, which therefore may be more clinically acceptable and tolerated in persistent pain populations. The primary aim of both randomised controlled trials (RCT) is to investigate the efficacy and acceptability of using high-frequency, low-load BFR-RT in UK military personnel with lower limb MSKI where persistent pain is the primary limiting factor for progression.

**Methodology:**

The presented protocol is a two-phase RCT based within a military rehabilitation setting. Phase One is a 1-week RCT to determine the most efficacious and acceptable BFR-RT protocol (7× BFR-RT sessions over 5 days at 40% or 80% LOP; n=28). Phase Two is a 3-week RCT comparing the most clinically acceptable BFR pressure, determined by Phase One (21× BFR-RT sessions over 15 days; n=26) to usual care within UK Defence Rehabilitation residential rehabilitation practices. Outcomes will be recorded at baseline, daily and following completion of the intervention. The primary outcome will be the brief pain inventory. Secondary outcomes include blood biomarkers for inflammation and pain (Phase Two only), injury-specific outcome measures, lower extremity function scale, objective measures of muscle strength and neuromuscular performance, and pressure pain threshold testing.

**Ethics and dissemination:**

The study is approved by the Ministry of Defence Research Ethics Committee (2318/MODREC/24) and Northumbria University. All study findings will be published in scientific peer-reviewed journals and presented at relevant scientific conferences.

**Trial registration number:**

Registered with Clinical Trials. The registration numbers are as follows: NCT06621914 (Phase One) and NCT06621953 (Phase Two).

STRENGTHS AND LIMITATIONS OF THIS STUDYThis novel two-phase study is based within a military residential rehabilitation setting with real-world outcomes and implications.Our two-phase study compares high versus low pressure blood flow restriction with resistance training (BFR-RT) over a 1-week period, to assess the acceptability and efficacy, before implementing the most accepted and efficacious pressure during a 3-week rehabilitation intervention where BFR-RT and usual care are compared with usual care alone.Our study combines objective (eg, neuromuscular strength, pressure pain threshold and temporal summation, blood biomarkers) and subjective (eg, patient-reported outcome measures) outcome measures to assess the acceptability, effectiveness and tolerability of BFR-RT.Our study only includes short-term follow-ups due to the nature of the studies, and the setting it is embedded within (ie, quick deployment upon return to home-unit).

## Background

 The occupational requirements for serving military personnel include exposure to extreme, arduous and unpredictable environments, increasing the risk of musculoskeletal injury (MSKI).^1 2^ Within the UK military, MSKI is the leading cause of medical downgrading (ie, medically limited deployable or medically non-deployable) and discharge.^3^ Subsequently, this negatively impacts operational readiness and increases the demand on Defence Rehabilitation services, both at a substantial economic cost to the UK Ministry of Defence.^4 5^ Within the UK military, the greatest incidence of MSKI occurs at the lower limb,^1 6^ with lower limb MSKI medical discharge rates varying between 31 and 42% in 2022/2023.^7^ Pain is often considered a primary limiting factor to rehabilitation progress following MSKI, further delaying return-to-operational duty.^8^,^10^ Persistent pain is considered a frequent contributing factor to the rates of many MSKI-related medical downgrades/discharges across military populations.^3 11^

Persistent pain (defined as pain lasting >3 months)^12^ can occur innocuously (eg, fibromyalgia) or following injury (eg, post-surgical), resulting in pathology-specific pathophysiological changes that can cause life-changing, prolonged disability and loss of function, and poor long-term prognosis.^13 14^ Moreover, the development of persistent pain involves abnormal somatosensory processing in the central and/or peripheral nervous system.^15^ MSKI and associated pain and/or persistent pain are often associated with altered motor drive,^16^ kinesiophobia^17^ and symptomatic impairment,^18^ thus reducing rehabilitation potential, increasing recovery time and associated financial costs.^5^

UK Defence Rehabilitation currently offers 2-week and 3-week residential/inpatient rehabilitation courses at regional rehabilitation units, and the Defence Medical Rehabilitation Centre (DMRC), Stanford Hall, for more complex and/or chronic musculoskeletal conditions, including persistent pain populations. Residential rehabilitation courses are interdisciplinary in nature and have demonstrated efficacy for improving clinical outcomes in a wide array of MSKI.^19^,^21^ Rehabilitation outcomes are assessed against the physical employment standards with an increasing emphasis on the restoration of muscle strength and power alongside aerobic and anaerobic capacity, ensuring military personnel are physically prepared to tolerate and meet the physical demands of their occupational role.^22^

Within traditional rehabilitation settings, heavy-load resistance training (RT; ie, loads >70% 1-repetition maximum (RM)) is often mandated to develop muscular hypertrophy and strength to improve function following MSKI.^23 24^ However, persistent pain can create symptomatic impairment and thus contraindicate the use of heavy-load RT due to the risk of further injury and/or worsening of symptoms.^25 26^ An individual’s inability to produce high quantities of force or apply force rapidly due to MSKI and/or persistent pain prolongs the rehabilitation timeframe and leads to failure to meet the essential physical employment standards for UK military personnel.^5 22^ In addition, following an MSKI and/or persistent pain, a decrease in physical function and reduction in physical activity levels can occur, leading to progressive, disuse-induced atrophy of skeletal muscle.^27^ Consequently, a negative feedback loop occurs, whereby decreased functional status and physical activity levels promote further exacerbation of symptoms (eg, persistent pain, and movement-evoked pain) and skeletal muscle atrophy,^27 28^ further prolonging the duration of rehabilitation and risk of secondary health conditions.^29^

To combat the dearth of exercise rehabilitation interventions that attenuate pain, a proactive three-pronged approach is employed by Defence Medical Services (ie, detection, prevention and treatment).^30^ Defence Medical Services practitioners identified 11 research topics that should be prioritised, including novel and innovative treatments (eg, blood flow restriction (BFR) exercise), pain management in rehabilitation, rehabilitation outcomes and residential/inpatient treatment paradigm.^31^ Recent research suggests that BFR exercise can elicit hypoalgesia,^32^,^34^ as well as promote favourable physiological adaption in load-compromised populations.^35^,^37^ Ladlow *et al*^21^ reported comparable changes in muscular strength and hypertrophy following two times per day low-load RT with BFR (BFR-RT) when compared with traditional heavy-load RT, as well as a significant reduction in pain (BFR group only) in UK military personnel with lower limb MSKI, highlighting the efficacy of implementing BFR-RT within a military inpatient setting. Additionally, Mason *et al*^38^ investigated intensity-matched and volume-matched BFR versus a non-BFR group in active military personnel who had knee surgery (meniscal repair or chondral restoration) and reported a reduction in within-session anterior knee pain following BFR-RT, and comparable changes in patient-reported function and strength measures.

Hughes *et al*^33^ reported significant reductions in knee pain during and 24 hours following BFR-RT, but not traditional RT, throughout an 8-week intervention following anterior cruciate ligament reconstruction. Additionally, following 12 weeks of two times per week BFR-RT, a significant reduction in pain was noted in a knee osteoarthritis cohort.^35^ Furthermore, Giles *et al*^32^ reported a greater reduction in pain (p=0.02) during activities of daily living following 8 weeks of three times per week BFR-RT sessions compared with a traditional heavy-load RT control group in patients with anterior knee pain. Research specifically investigating BFR-induced hypoalgesia is still within its infancy and has been extrapolated from the work of exercise-induced hypoalgesia (EIH).^39 40^ However, to elicit an EIH response through traditional exercise modalities, high-intensity effort and/or longer durations of exercise are typically required (eg, >75% 1RM),^41^ which is often not feasible for load-compromised and/or persistent pain populations due to self-immobilisation and symptomatic impairments.^25 26^ The hypoalgesic response reported following BFR-RT occurs following low-load (20–30% 1RM) exercise.^32 33 35^ It has been proposed that a combination of factors accounts for the hypoalgesic response seen following BFR exercise, with the activation of opioid and endocannabinoid systems, conditioned pain modulation, high threshold motor unit recruitment, simulation of baroreceptors, and local mechanisms (eg, autoregulation of chemokine pathways, exercise metabolite accumulation, mast cell degranulation, and upregulation of anti-inflammatory cytokines), all being cited.^39 40 42^ Hughes *et al*,^43^ and Hughes and Patterson,^44^ reported a greater hypoalgesic response following low-intensity BFR exercise with a high pressure (ie, 80% of limb occlusion pressure (LOP)) compared with a lower pressure (ie, 40% LOP), and low-intensity exercise without BFR, suggesting a possible dose-response relationship between the pressure applied and magnitude of the hypoalgesic response. An acute increase in beta-endorphin, an endogenous neuropeptide, was reported in healthy participants following BFR-RT; however, at 24 hours, beta-endorphin levels were comparable to baseline, despite a local hypoalgesic response still being evident, suggesting that alternative mechanisms mediate BFR-induced hypoalgesia.^43 44^ This research supports the notion that local mechanisms play a substantial role in the hypoalgesic response of BFR exercise.^42^ Conversely, the EIH response is often inconsistent within persistent pain populations,^45^ with exercise sometimes eliciting hyperalgesia.^46^

A scarcity of literature is currently available concerning the impact of the applied pressure (ie, LOP) and BFR-induced hypoalgesia effect. The acceptability and tolerance of higher relative BFR pressures in persistent pain populations are also unknown due to the complexity of presentation (eg, hyperalgesia) and the perception of discomfort experienced during BFR exercise.^47 48^ Research currently suggests that greater pressures (ie, 80% LOP) elicit a greater hypoalgesic response in response to a noxious stimulus in pain-free individuals;^43 44^ however, if greater pressures are not tolerated, the opportunity to promote hypoalgesia could be lost, and it is currently unknown whether higher pressures elicit a greater acute hypoalgesic response in individuals with pain/persistent pain. Additionally, lower relative pressures (ie, 40% LOP) have elicited a statistically significant hypoalgesic response in pain-free individuals,^43 44^ which therefore may be more clinically acceptable and tolerated within persistent pain populations. Within UK Defence Rehabilitation residential rehabilitation courses, physiotherapists and exercise rehabilitation instructors only get a limited period per day with injured personnel; therefore, leveraging short-term pain reduction from BFR-RT may allow additional exercise rehabilitation activities to occur, akin to the work by Hughes *et al*,^33^ Korakakis *et al*^49^ and Ladlow *et al*.^21^ The clinical and mechanistic (biomechanical and neuromuscular) underpinnings of high-frequency BFR-RT in UK military personnel with persistent knee pain are currently being investigated at multiple regional rehabilitation units.^50^ However, this study does not directly measure mechanisms of pain modulation.

Any intervention that can accelerate the progression of complex MSKI rehabilitation and ameliorate pain, while exercising at a lower relative training intensity, is of interest to UK Defence Rehabilitation services.^50^ Research investigating the efficacy and acceptability of different BFR training interventions during the rehabilitation of military personnel with lower limb MSKI primarily limited by pain is warranted. To develop our understanding of BFR-induced hypoalgesia and develop best practice guidelines, a pragmatic research study, embedded within a ‘real-world’ clinical setting, is proposed.

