### Sample size calculation

For both phases, the sample size calculation was based on the effect size for a significant and clinically meaningful reduction in patient-reported pain (ie, the primary outcome measure, the Brief Pain Inventory (BPI))^54^ and calculated using G Power V.3.1.9.6.

Phase One: using a repeated measures analysis of variance (ANOVA; between factors) sample size calculation with an effect size of d=0.64,^54^ power=0.95, alpha=0.05, considering two treatment arms and three measurements timepoints (ie, pre-intervention and post-intervention, and follow-up), the required sample size is 24 patients. However, to account for a 10% drop out (as guided by previous ADMR publications^50 55 56^), a minimum of 28 patients will be recruited (n=14 per study arm).

Phase Two: using a repeated measures ANOVA (between factors) sample size calculation with an effect size of d=0.64,^54^ power=0.95, alpha=0.05, two treatment arms, and four measurements timepoints (ie, pre-intervention, end-week 1 intervention, end-week 2 intervention and post-intervention), the required sample size is 22 patients. However, to account for a 10% drop-out, 26 patients will be recruited (n=13 per study arm).

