### Experimental intervention

During the first week of the residential rehabilitation course, participants in both groups will replace standardised knee dominant exercise with low-load BFR-RT at either low (ie, 40% LOP) or high (ie, 80% LOP) pressure, with previous literature reporting significant hypoalgesia following BFR exercise at both high and low pressures.^43 44^ Both experimental groups will complete seven BFR-RT sessions over the first week of the residential rehabilitation course (Monday–Friday). Using the Personalised Tourniquet System for BFR (Delfi Medical Innovations Inc, Vancouver BC, Canada), with an Easi-Fit BFR Cuff (single-bladder, contoured) fully encircling the limb and matching limb protection sleeve (24″×4.5″ or 34″×4.5″, dependent on limb size), each session will consist of a unilateral leg press exercise (Technogym, Bracknell, UK), followed by unilateral knee extension exercise with ankle weights (Komodo Sports, Huntingdon, UK), on the affected limb. The Personalised Tourniquet System for BFR automatically measures the individual’s LOP while at rest in supine (20–350 mm Hg±6 mm Hg of a set-point, 10 s average under non-transient conditions), which literature reports as a valid and reliable measure;^57^,^59^ thereafter, either 80% LOP (BFR80) or 40% LOP (BFR40) will be used based on the participants’ assigned group. Participants will complete 1 set of 30 repetitions, followed by 3 sets of 15 repetitions at 20% 1RM, with 30 s rest between sets (continuous inflation during exercise) and a 3 min reperfusion period between exercises. Both exercises will be performed using a 1:0:1 tempo (1 s concentric phase, no pause and 1 s eccentric phase). On the Wednesday and Thursday of the intervention week, BFR-RT will be performed twice daily, with sessions separated by >4 hours.

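### Phase One's 95% power rests on an effect size that the protocol does not support for a comparison of 80% with 40% LOP

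*Protocol article*

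**What the plan says.** The Sample size calculation section gives one basis for both phases: "the effect size for a significant and clinically meaningful reduction in patient-reported pain", measured by the BPI. The same value from the same citation then enters two calculations:

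- "Phase One: using a repeated measures analysis of variance (ANOVA; between factors) sample size calculation with an effect size of d=0.64", with "power=0.95, alpha=0.05, considering two treatment arms and three measurements timepoints". The result is 24 patients, or 28 after 10% dropout. This phase compares 80% with 40% LOP.
- "Phase Two: using a repeated measures ANOVA (between factors) sample size calculation with an effect size of d=0.64", with "power=0.95, alpha=0.05, two treatment arms, and four measurements timepoints". The result is 22 patients, or 26 after dropout. This phase compares BFR with usual care.

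No separate basis is given for the size of the gap between the pressures. The Phase One Experimental intervention section supports both arms by "previous literature reporting significant hypoalgesia following BFR exercise at both high and low pressures". The Background ties the evidence for the lower pressure to people without pain ("lower relative pressures (ie, 40% LOP) have elicited a statistically significant hypoalgesic response in pain-free individuals"). It adds that a greater acute response to higher pressure in people with pain is not established.

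**The concern.** A meaningful reduction in pain describes what a treatment achieves. The difference between two pressures, each expected to do something, is another quantity. On the protocol's own rationale it is likely to be the smaller one, since part of any benefit would be common to both arms. Using the same 0.64 for it, without argument, makes the stated power depend on a large gap for which the article offers no evidence.

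This matters because significance on the BPI steers the choice for Phase Two. Under the Phase Two Experimental intervention section, a non-significant BPI difference moves the decision to the LEFS and, failing a difference there, to the lower pressure. A reader who trusts the 95% would take a null BPI result as a well-powered finding of no difference.

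**Working it through.** **Inputs from the protocol article.** Effect size 0.64, labelled d; alpha 0.05; two arms; m=3 visits in Phase One and m=4 in Phase Two; N=24 and 22 before dropout; 10% dropout (Sample size calculation). Two-sided tests (Statistical methods and analysis). Allocation 1:1 (Randomisation and blinding procedure).

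**Assumed.** The correlation ρ between visits is not given. I use 0.5 and show 0 to 0.8 where it matters.

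**Formula** (repeated-measures ANOVA, between factors): λ = f²·N·m / (1+(m−1)ρ), with F on 1 and N−2 degrees of freedom. For two equal groups f = d/2, where d is the difference in SDs of a single-visit score.

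**1. The plan's own figures.** Taking 0.64 as f, with ρ=0.5:

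- Phase One: λ = 0.4096·24·3/2 = 14.75, power 95.6%. N=24 is reproduced.
- Phase Two: λ = 0.4096·22·4/2.5 = 14.42, power 95.0%. N=22 is reproduced.
- Dropout: 24/0.9 = 26.7 and 22/0.9 = 24.4, so 27 and 25, which become 28 and 26 in equal arms.

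But f=0.64 corresponds to d=1.28. Power of exactly 95% with 24 patients needs f=0.629, that is, a gap of about 1.26 SD.

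**2. With 0.64 as a true d** (f=0.32), ρ=0.5:

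- Phase One, N=24: λ = 0.1024·72/2 = 3.69, power 45%. For 95% power, N would be 88.
- The same at ρ=0: λ = 7.37, power 74%. At ρ=0.8: λ = 2.84, power 36%.
- Phase Two, N=22: λ = 0.1024·88/2.5 = 3.60, power 44%. For 95% power, N would be 82.

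**3. Phase One power over a range of gaps** (ρ=0.5). The gaps are illustrative, because the article gives no value for 80% versus 40% LOP.

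| Gap, f | Gap, d | Power, N=24 | Power, N=28 |
|---|---|---|---|
| 0.64 | 1.28 | 96% | 98% |
| 0.48 | 0.96 | 79% | 85% |
| 0.32 | 0.64 | 45% | 51% |
| 0.24 | 0.48 | 28% | 32% |
| 0.16 | 0.32 | 15% | 17% |

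**4. Gap detectable at 80% power.** Solving for d: d = 2·√[λ(1+(m−1)ρ)/(N·m)], with λ the value that gives 80% power.

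- Phase One, N=24 (λ=8.59): 2·√(8.59·2/72) = 0.98 SD at ρ=0.5; 0.69 SD at ρ=0; 1.11 SD at ρ=0.8.
- Phase One, N=28 (λ=8.47): 2·√(8.47·2/84) = 0.90 SD at ρ=0.5.
- Phase Two, N=22 (λ=8.68): 2·√(8.68·2.5/88) = 0.99 SD at ρ=0.5.
- Phase Two, N=26 (λ=8.53): 2·√(8.53·2.5/104) = 0.91 SD at ρ=0.5.

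**The case against.** A reader might infer that the two uses of 0.64 contradict each other. Let a and b be the effects of 40% and 80% LOP over usual care. Phase One sets b−a=0.64. If 80% goes forward, Phase Two sets b=0.64, which would leave a=0 and an inert lower pressure. The documents do not support that inference, for four reasons:

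- The value is described as a clinically meaningful reduction, which can be read as a target, and one target can size two trials.
- If 40% goes forward, a=0.64 and b=1.28 are consistent.
- If 80% goes forward and 40% has some effect, b exceeds 0.64 and Phase Two's assumption is merely conservative.
- The phases last one and three weeks, so their effects need not be equal.

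It would also go too far to say that the protocol establishes 40% LOP as active on the BPI. The cited evidence concerns pain-free people, and the Background notes that responses to exercise in persistent pain are inconsistent. The source of 0.64 is not shown, so what it measures cannot be settled here. The smaller gaps in the table are illustrative, and any trial loses power when the true effect is below the planned one.

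The article also tempers its claims. It calls Phase One a pilot, admits that small samples risk type I and II errors, and plans 95% CIs. A null BPI result does not choose the pressure alone, because the LEFS comes next.

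All of this stands against the charge of contradiction. It does not supply a basis for the Phase One gap or correct the stated 95%. Not knowing whether higher pressure does more in patients is itself a reason not to assume a large gap.

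**Conclusion.** The point holds as one of unsupported power. The article carries a single effect size over to a comparison of two pressures, gives no reason to expect a gap that large, and attaches 95% power to it. At ρ=0.5 that figure needs a gap of about 1.26 SD. At a true d of 0.64, as labelled, power with 24 patients is about 45% (36% to 74% for ρ from 0.8 to 0), and at d=0.32 about 15%. Part of the shortfall arises because the stated N follows only if 0.64 is used as f. Correcting that label alone would still leave the between-pressure gap unjustified. The same scale problem affects Phase Two, where power at a true d of 0.64 is about 44% with 22 patients. The figures rest on the assumed visit correlation and on the between-factors routine that the article names. The sample sizes and the design need not change.

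**What to change.** In the Sample size calculation section:

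- **Phase One:** drop the claim of 95% power at d=0.64 and keep n=28. State the between-pressure BPI difference detectable at 80% power: about 0.98 SD with 24 patients and 0.90 SD with 28 at a correlation of 0.5, and 0.69 to 1.11 SD with 24 for correlations of 0 to 0.8.
- **Phase Two:** do not keep 95% power at d=0.64. Restate it on the same scale: about 0.99 SD with 22 patients and 0.91 SD with 26, at 80% power and a correlation of 0.5.

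Where the choice of pressure is described (Phase Two, Experimental intervention), add that a non-significant BPI result is not evidence that the pressures are equivalent. Interpret Phase One through the BPI difference and its 95% CI, which the Statistical methods section already plans.

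The cost is a few sentences and a less favourable power statement for both phases. No extra patients are needed.
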